### Intervention and comparator

#### Psychosocial Treatment-As-Usual (TAU)

A manual ([name], [name], [name], [name], [name], [name], [name]: Manuel du traitement psychiatrique intégré (Treatment-as-usual) du patient déprimé hospitalisé, Unpublished manuscript, Institute for Psychotherapy, Centre Hospitalier Universitaire Vaudois and University of Lausanne; 2007) which follows the Practice guideline for the treatment of patients with Major Depression of the American Psychiatric Association [2], contains all the treatments and procedures offered to patients. Treatment includes: (1) A first interview of 45 minutes to define a treatment plan made up of patient’s, nurses’, medical, and social objectives. Therapeutic staff meets once a week to adapt it; (2) Supportive interventions of 20 to 25 minutes (clinical management), addressing psychopharmacological issues when necessary, delivered twice a week by a psychiatric resident; (3) Weekly two 30-minute encounters with nurses aiming at developing the patient’s psycho-educational skills, empowerment, and individualized treatment; (4) 6 psychoeducation group sessions; (5) Social workers, ergo-, physio-, and art-therapist interventions integrated into the treatment as required by the patient’s needs; (6) Pharmacotherapy following the rules of the World Federation of Societies of Biological Psychiatry [35].

#### Inpatient Brief Psychodynamic Psychotherapy (IBPP)

Our manualized intervention model proposes a brief psychodynamic intervention program in 12 sessions over 4 weeks ([name], [name], [name]: Traitement psychodynamique bref de la dépression pour patient hospitalisé, Unpublished manuscript, Institute for Psychotherapy, Centre Hospitalier Universitaire Vaudois and University of Lausanne; 2008). Sessions are 45 minutes long. It is based on the Bush, Rudden & Shapiro (2004) manual of psycho-dynamic treatment of depression to help the therapy focalize on relevant depression foci [36]. For transfe-rence, personality organization and conflictual themes the intervention is based on [name], Michel, & [name] (2010) manual on brief psychodynamic psychotherapy. Both manuals were adapted to the brief inpatient setting [37]. Put briefly, the 12-session psychotherapy approaches the crisis in the patient’s intrapsychic and interpersonal equilibrium that led to a hospital admission, within the context of depression [38]. It focuses on both the patient’s conscious and unconscious motives for admission. The initial hypothesis is based on the dynamic relationship established between the therapist and the patient during the first three sessions (pre-transference), on the patient’s present crisis, and on the dynamics that form the core of his/her depressive episode. Following sessions focalize further on helping the patient to gain a better understanding of the psychological factors that led to the emergence of depressive symptoms and to address his/her vulnerability to those dynamics. Final sessions address the patient’s feelings and fantasies about termination as well as the decision regarding a therapy of longer duration or long-term psychiatric treatment if necessary.

### Outcome measures

As recommended in meta-analytic reviews, various broad areas of patient’s functioning are assessed including (1) psychopathology, (2) personality, social role and quality of life, and (3) dynamic functioning which may underlie impaired functioning and contribute to vulnerability to psychiatric disorders [33]. Validated French version is available for each of the following questionnaires. Questionnaires are filled in with the help of a research assistant. Due to their depressive symptomatology, patients may face some difficulties with self-report questionnaires. Therefore we have restricted the total number of items included in the assessment battery.

#### Psychopathology

##### Depression

Depressive symptoms are the primary outcome. This is assessed by two instruments: (1) The Montgomery-Asberg Depression Scale (MADRS; [39]), a clinician rating measure in 10 items, which serves as our primary outcome measure, and (2) the self-rated version of the Inventory of Depressive Symptom (QIDS-SR_16_; [40]), a 16-item self-report measure of depressive symptoms. To allow for Kaplan-Meyer estimates of speed of response, MADRS is done on a weekly basis. The Depressive Experience Questionnaire (DEQ; Blatt SJ, D’Afflitti J, Quinlan DM: Depressive Experiences Questionnaire, Unpublished research manual, Yale University; 1979) assesses a wide range of life experiences often reported by depressed individuals but not considered symptoms of depression. Its well-established factor structure measures two primary dimensions: interpersonal relatedness and self definition.

##### Distress

The Brief Symptom Inventory (BSI; [41]) derived from the Symptom Check-List (SCL-90-R) is a widely used self-report measure of distress and psychiatric symptoms; the Global Assessment of Functioning (GAF) is a numeric scale (0 through 100) used by an independent coder to rate the social, occupational and psychological level of functioning.

##### Diagnosis

The Diagnostic Interview for Genetic Studies (DIGS; [42]) is used to collect diagnostic information. This instrument enables the collection of extensive information on the course of psychiatric conditions including mood and anxiety disorders. An updated version of the DIGS includes DSM-IV criteria [43]. The reliability of the French version was established in Lausanne for major mood and psychotic disorders [44].

##### Early trauma

Early childhood trauma is recognized as the best predictor of response to psychotherapy for severely depressed patients [45]. The childhood Trauma Questionnaire Short-Form (CTQ-SF; [46]) provides a quick, multidimensional, retrospective measure of childhood trauma with sound reliability and validity characteristics.

##### Emotions

Measured prior to therapy, alexithymia was shown to be the best predictor of residual symptoms in depressed patients who respond to short-term psychotherapy [47]. Alexithymia and other problematic patterns of emotion processing is assessed by the Dimensions of Emotional Openness (DOE; [48]).

#### Psychosocial role functioning

##### Interpersonal problems

The Inventory of Interpersonal Problems (IIP; [49]) is a self-report measure of problems in interpersonal relationships, which is widely used in psychotherapy research. We use the short version in 12 items and the main outcome is the total item-mean [50].

##### Social adjustment

The Social Adjustment Scale Self-Report (SAS-SR; [51]) assesses six areas of functioning including work, social and leisure, extended family, intimate relations (e.g., spouse), parents, and family unit, each on a six-point scale.

#### Dynamic personality functioning

##### Psychodynamic diagnosis and change

The Operationalized Psychodynamic Diagnosis is a form of multiaxial diagnostic system based on five axes: I = experience of illness and prerequisites for treatment, II = interpersonal relations, III = conflict, IV = structure and V = mental and psychosomatic disorders [52]. To measure change in this domain, we use the Heidelberg Structural Change Scale (HSCS). Studies on content, criterion, and construct validity indicate good validity for the individual axes [53].

##### Defensive functioning

The Defense Mechanism Rating Scales (DMRS; [54]) is an observer-rated method for quantitative ratings of 28 defense mechanisms. The Overall Defensive Functioning (ODF) score then summarizes the adaptive level of defensive functioning, which is capable of detecting change over time, and predicts improvement in major depressive episodes [55].

##### Therapeutic alliance

Inpatient setting requires differentiating between two different forms of alliance. Alliance with the individual therapist is assessed by the short form of the Working Alliance Inventory Short-Form (WAI-SF) in a revised version [56]. Alliance with the treatment team is assessed by the Inpatient Treatment Alliance Scale (I-TAS; [57]). For both instruments, we use the patient self-rated version.

#### Cost-effectiveness data

Collection and management of the economic data are fully integrated into the clinical data. Data will be assessed at baseline (by ad hoc retrospective questionnaire), discharge (1 month), and at follow-up after 3 months and 12 months. Measures include:

##### Costs

Information will be collected on inpatient and outpatient direct costs (hospitalizations, emergency department visits, outpatient psychiatrist, psychotherapist, physician, and other health care providers, and psychotropic and nonpsychotropic prescriptions) and indirect costs (productivity loss).

#### Quality of life (cost-utility analysis)

European Quality of Life-5 dimensions (EQ-5D) is a short standardized patient-rated instrument measuring health-related quality of life. The EQ-5D provides two important aspects: a descriptive profile based on five dimensions including mobility, self-care, usual activities, pain/discomfort, anxiety/depression, and a valuation of the profile by a visual analogue scale (EQ VAS).

#### Follow-up data (after 3 and 12 months)

Following termination of the active phase of treatment (after the 4 weeks of psychotherapy or at discharge from hospital), the vast majority of the patients are referred to an outpatient unit for additional treatment or referred to appropriate clinical services. In addition to the questionnaires, data is gathered concerning symptomatology, the type and dose/frequency of pharmacological and psychosocial ambulatory treatments, re-hospitalizations using the Longitudinal Interval Follow-up Examination (LIFE; [58]).

### Treatment integrity

#### Recording and transcription

All individual therapy sessions are audiotaped. Selected sessions (1 early session – between Ss 2 to 4 and 1 late session – between Ss 8 to 11) will be transcribed using a standardized transcription method [59]. Adherence and competence to IBPP will be assessed on selected sessions with the following instruments: (1) The *Psychotherapy Process Q-Set* (PQS ; Jones EE: Manual for the Psychotherapy Process Q-set. Unpublished manuscript, Berkeley, CA: University of California; 1975; [60]), a rating scale assessing characteristic elements of a therapeutic session. which can be compared with the ideal prototype of specific therapeutic methods (i.e., psychoanalytic, cognitive-behavioral, family-systemic, brief psychoanalytic) An expert PQS prototype specific to the IBPP will be developed and compared to the interpersonal and CBT prototypes [61]; (2) The *Psychodynamic Intervention Rating Scale* (PIRS; Cooper S, Bond M: Manual for the Psychodynamic Intervention Rating Scale, Unpublished manuscript. Montreal: Institute of Community and Family Psychiatry, Sir Mortimer B. Davis - Jewish General Hospital; 2006), an instrument elaborated specifically to investigate psychoanalytic psychotherapies. It allows to distinguish interpretative interventions from other types of intervention, and to assess the depth of understanding of interpretations on a five-point scale.

#### Therapists’ selection and training

All psychotherapists (N between 10 and 15) are resident psychiatrists in an advanced or completed stage of a 4-year psychotherapy training program in psychodynamic psychotherapy and having attended training in brief psychodynamic psychotherapy and IBPP. The IBPP training course lasts two years (two hours weekly). The first year includes theoretical presentation, role playing and case presentation. The second year is devoted to group supervision. Training is delivered by three expert trainers of the Lausanne University Medical School, who are agreed supervisors for the psychodynamic psychotherapy and authors of the IBPP manual.

#### Supervision

For the IBPP group, each therapist benefits from one individual supervision each week, delivered by the same three expert therapists that give the training. For the TAU group, each psychiatrist will benefit from one hour of individual supervision each week carried out by an experienced psychiatrist of the unit.

### Procedure

#### Data collection site

The hospital section specialized for the treatment of mood, anxiety and personality disorders is a 40-bed unit, which is part of the Department of Psychiatry of the University of Lausanne. Patients are treated in a time-limited program (mean duration stay = 26.2 days; median = 20 days). This period is considered sufficient to work through the crisis situation and its determinants and to provide for adequate follow-up treatment referral when necessary. The length of the patient stay is determined by the clinical staff, independently of the research, i.e. the time of discharge does not depend on the completion of psychotherapy, or after one month for the comparison group. Only the post-treatment measurement will be after one month, which is anyway close to the mean patient stay (26.2 days).

#### Patients recruitment

All patients hospitalized in the clinical unit with a diagnosis of major unipolar depression are referred to the project, interviewed for eligibility by a research assistant (RA) and then given the intake assessment battery. Patients giving informed consent (to be randomly assigned to one of the treatment settings; to participate in the diagnostic and psychometric procedure; to agree, if necessary, that psychotherapy sessions are audio recorded; and to take part in the follow-up measurements) are then randomized in one of the two treatment groups. Assessment with the same instruments are also done after one month of treatment (in a in- or partially out-patient setting), then after 3 months and 12 months follow-up. Cases will be considered as dropout if they had less than 5 sessions. Study is currently continuing follow-up. It is closed to recruitment of participants (as of June 2012).

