### Power calculation

Based on previous studies, at least moderate effect sizes of psychodynamic psychotherapy on patient outcome (e.g. f = .25 for severity of depressive symptomatology) could be expected. Power analysis (with two-tailed alpha set at .05 and a power of .80) for repeated measure ANOVA indicates that 108 patients (54 in each group) are sufficient to detect the expected effects [34]. With 22% of non-completers, an *intent-to-treat sample* of 138 patients (69 in each group) is required in order to have a *completer sample* of 108 patients. All analysis will be done on the two samples.

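### The only completer rule given, at least 5 sessions, naturally fits the IBPP arm alone, so the planned completer comparison may set a selected arm against an unselected one

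*Protocol article*

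**What the plan says.** Under Patients recruitment the protocol article states: "Cases will be considered as dropout if they had less than 5 sessions". It names no arm and does not define a session.

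Under Power calculation the trial is sized on 108 completers, 54 per group. This is raised to 138 randomised, 69 per group, to allow for 22% non-completers. The section ends: "All analysis will be done on the two samples".

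The IBPP section describes "a brief psychodynamic intervention program in 12 sessions over 4 weeks". The TAU section describes contact in other terms: supportive interventions "delivered twice a week by a psychiatric resident", and "Weekly two 30-minute encounters with nurses". Neither has a required total. The one TAU item counted in sessions is "6 psychoeducation group sessions". The Strengths and limitations section says that IBPP is given on top of TAU, so both arms are offered those groups.

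Under Data collection site, clinical staff decide discharge, and "the time of discharge does not depend on the completion of psychotherapy". The median stay is 20 days. The Data analysis section puts the final analyses on an intention-to-treat basis, by randomised group.

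**The concern.** A session count works as an attendance threshold for IBPP. TAU has no matching count, so on the natural reading the rule cannot exclude a TAU patient. The completer comparison would then set IBPP patients who stayed in therapy against all TAU patients.

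Session attendance is observed after randomisation and may depend on how the patient is doing. Some patients may stop because they feel better or go home, others because they worsen or refuse. A TAU patient with the same course would be kept. That breaks the balance that randomisation provides. Because every analysis is repeated on this sample, each outcome would carry a second contrast exposed to this selection.

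**Working it through.** **1. The plan's own figure.** Randomised number = completers / (1 − non-completion) = 108 / 0.78 = 138.5, against 138 stated. Per arm, 69 × 0.78 = 53.8, or 54. The inflation reproduces, and it assumes equal loss in both arms. The base of 108 can be reached for f = 0.25, but only with a number of measures and a correlation that the article does not give. For example, the between-group repeated-measures test needs 108 with 3 measures and a correlation of 0.75, or with 5 measures and 0.8.

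**2. What the stated rule yields if it can act on IBPP only.**
- 22% of the IBPP arm removed: 69 × 0.78 ≈ 54 IBPP against 69 TAU, total 123.
- 22% of all 138 removed, all from IBPP: 138 × 0.22 ≈ 30 patients, or 30.4 / 69 = 44% of that arm. About 39 against 69 remain.

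Neither gives 54 against 54. The problem in the first case is not lost power. The information term n1·n2/(n1+n2) is 54 × 69 / 123 = 30.3, against 54 × 54 / 108 = 27. The problem is comparability.

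**3. Would counting TAU contacts repair it?** IBPP runs at 12 / 4 = 3 sessions a week, so the fifth falls near day 5/3 × 7 = 11.7. Twice-weekly resident contacts reach five near day 5/2 × 7 = 17.5. The same count would mark different exposure in the two arms. Counting the psychoeducation groups is possible in both arms, but the text does not say so.

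**4. Size of the possible bias (illustration).** Assumptions: no true effect, 69 per arm, the lowest 22% on a normal attendance variable removed from IBPP only, and correlation r between that variable and outcome. The documents give no value for r.

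Shift = r × φ(z₀.₂₂) / 0.78 = r × 0.296 / 0.78 = 0.38 r, in SD units. The standard error of the contrast is √(1/54 + 1/69) = 0.182 SD. The false-positive rates come from 6,000 simulated trials per setting, with a two-sided t test at 0.05.

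| r | Shift (SD) | False-positive rate, IBPP filtered only |
|---|---|---|
| 0 | 0 | about 5% |
| 0.2 | 0.08 | 7.1% |
| 0.3 | 0.11 | 9.7% |
| 0.5 | 0.19 | 18.1% |

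With the same filter in both arms the shift is about 0 and the rate is 4.7 to 5.4%. The planned effect f = 0.25 corresponds to d = 2 × 0.25 = 0.5, so 0.08 to 0.19 SD is 16 to 38% of it. The sign follows the direction of the association. Losing patients who do badly flatters IBPP, and losing early improvers works against it.

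**The case against.** Several counter-arguments have force.

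- **The one-arm filter is inferred.** The rule names no arm and does not say that a dropout is a non-completer in the sense of the power section. The equal planned loss suggests that the authors expected TAU non-completers. This stands as a limit on certainty. However, no other completer rule is given, and the one given does not show how a TAU patient could fail it.
- **A condensed article may leave such detail to the full protocol.** This would answer a complaint that a definition is absent. Here the article does state a rule, a sample and an equal split, and on the natural reading these do not fit together.
- **A reader might infer that the completer result has equal standing with intention-to-treat.** The document does not support that. The Data analysis section already makes the final analyses intention-to-treat. The power section says only that both samples are analysed, without ranking them.
- **A reader might infer that early discharge ends therapy and so creates dropouts.** That is not established. The recruitment section allows the month of treatment to be partly outpatient, so sessions may continue after discharge.
- **A reader might infer that the completer result will favour IBPP.** This is also unsupported. Early improvers and patients who worsen push in opposite directions and may partly cancel.

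**Conclusion.** The concern holds in a limited form. The only completer rule in the article naturally applies to one arm. It then contradicts the planned 54 and 54, giving about 54 and 69, and it selects on a post-randomisation variable. The completer contrast can therefore be biased in either direction.

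The 0.08 to 0.19 SD shift and the 7 to 18% false-positive rate are illustrative. They rest on an assumed correlation of 0.2 to 0.5, on all 22% being lost from IBPP, and on the association running one way. If attendance is unrelated to outcome, there is no bias. The intention-to-treat result is untouched, so the defect is confined to the completer analyses and to the 54-per-arm completer basis of the sample size.

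**What to change.** 1. In the Power calculation section, state that the efficacy conclusion rests on the intention-to-treat sample alone and that the completer analysis is supportive.
2. Replace the session-count rule with one that applies identically in both arms, for example that the 1-month MADRS was obtained. Say openly that this too is a selection after randomisation: identical wording does not make the arms comparable if attendance at assessment depends on treatment.
3. If the effect in patients with at least 5 sessions is wanted, estimate it with randomisation as the instrument: the intention-to-treat difference divided by the share of IBPP patients with at least 5 sessions. State the assumption that fewer than 5 sessions has no effect. It is open to doubt, because the IBPP section treats the first three sessions as working sessions. If they do have an effect, the estimate could be inflated.

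The cost is a change of wording, one optional extra analysis and a less prominent completer estimate. The article reports recruitment closed and follow-up still running, so the analysis can still be amended.

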#### Randomization

Allocation to treatment groups is done using a stratified block randomization method with permuted block (available at http://www.randomization.com). Three stratification variables are used to ensure treatment balance [62]: age (two levels: x<=40<y), gender (two levels: M/F), and chronicity - that full criteria for a Major Depressive Episode have been continuously met for at least 2 years (two levels: Y/N).

#### Blinding

To guarantee allocation concealment, randomization was done by a totally independent researcher, and each allocation was given to the recruiting RA in a sealed envelope prior to seeing a new patient. The envelope was opened if and only if the patient is included in the protocol. Observers are blinded to treatment arm.

#### Rater training

DIGS are done by experienced raters working at the Epidemiology and Psychopathology Research Unit, directed by one co-applicant ([name]). Extensive training is provided for the MADRS (one hour weekly during three months) for the RAs. At the end of the training, an inter-rater reliability of at least ICC(2,1) > .75 should be reached. Inter-rater reliability will be calculated for 20% of the cases. All raters are blind of the clinical data.

### Data analysis

Final analyses will follow an intention-to-treat strategy comparing patients in the groups to which they were originally randomized. Clinical Significance method will be used to estimate rates of response (reliable improvement), remission (clinical significance), recovery (maintained clinical significance) and relapse (deterioration) [63]. For short-term outcome, repeated-measure analyses of variance (ANOVA) and analyses of covariance (ANCOVA - controlling for pretreatment scores and patient’s age) will be used on all outcome measures. For long-term outcome, linear mixed-effects models will be preferred, as well as for therapist and alliance effects on outcome [64]. Last Observation Carried Forward (LOCF) will be used for missing data when appropriate. Latent class analysis (using Latent Gold 4.5) will be done to explore the effect of moderating variables.

Cost-effectiveness analysis will be done in collaboration with the Institute of Health Economics and Management (IHEM) of the University of Lausanne. An economist at the IHEM will be in charge of the data analysis. The economic evaluation will be conducted from the perspective of the health system. Primary outcome will be remission in depressive symptomatology at 12 months. The comprehensively measured service costs between the two treatments will be compared with the difference in change in the primary outcome measure and with the difference between the treatments in QALYs gained.

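### The short-term ANCOVA adjusts for pretreatment score and age but omits gender and chronicity, two of the three stratification factors

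*Protocol article*

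**What the plan says.** The Randomization section of the protocol article describes a "stratified block randomization method with permuted block". It states that "Three stratification variables are used to ensure treatment balance" and lists them as "age (two levels: x<=40<y), gender (two levels: M/F), and chronicity", the last being whether full criteria for the episode have been met without a break for two years or more. Each factor has two levels, so there are 2 × 2 × 2 = 8 strata. The block size is not given.

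The Data analysis section names two short-term methods, a repeated-measures ANOVA and an ANCOVA. The ANCOVA is specified as "controlling for pretreatment scores and patient’s age", and the two methods "will be used on all outcome measures". Gender and chronicity appear in no stated model. For later time points the section says "For long-term outcome, linear mixed-effects models will be preferred", without naming covariates.

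**The concern.** An analysis should normally reflect the way patients were allocated. Stratified blocks make the arms alike on the stratification factors, so part of the outcome variance can no longer contribute to the difference between arms. A model without those factors still counts that variance as residual noise. The reported standard error then exceeds the true sampling variability of the estimate, confidence intervals are too wide and the test rejects too rarely under the null. This happens only if the omitted factors are prognostic given the covariates already in the model.

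Here the covariate list is written out, and it keeps one stratification factor while leaving out two. It is a stated choice, so it can be reviewed without the full analysis plan. The article also treats chronicity as clinically relevant: the Objectives include chronic depression in the target population, and the Background cites results specific to chronic forms. It does not say how strongly chronicity predicts outcome.

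At stake is a small amount of power and confidence intervals somewhat wider than the design warrants.

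**Working it through.** **Inputs from the article.** Three two-level stratification factors (Randomization); ANCOVA covariates pretreatment score and age (Data analysis); "with two-tailed alpha set at .05 and a power of .80" and 108 completers, 54 per group (Power calculation).

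**The plan's own figures.** 138 agrees with 108/(1 − 0.22) = 138.5 to within rounding. The 108 cannot be derived from the stated inputs alone, because the number of repeated measurements and their correlation are not given. This point does not dispute it: 80% power at 54 per group is taken as the starting point.

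**Assumed input.** R2 is the share of residual variance that gender and chronicity jointly explain after pretreatment score and age. The article gives no value, so 0 to 0.10 is shown.

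**Formulas**, with strata balanced by design, z(0.975) = 1.960 and z(0.80) = 0.842 (sum 2.802):

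- Ratio of reported to true standard error, factors omitted: 1/√(1 − R2)
- Type I error, factors omitted: 2 × [1 − Φ(1.960/√(1 − R2))]
- Power, factors omitted: Φ(0.842/√(1 − R2))
- Power, factors included: Φ(2.802/√(1 − R2) − 1.960)

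Example, R2 = 0.10: √0.90 = 0.9487, so the ratio is 1.054. Type I error is 2 × [1 − Φ(2.066)] = 0.039. Power omitted is Φ(0.887) = 81.3%. Power included is Φ(2.953 − 1.960) = Φ(0.993) = 84.0%.

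| Assumed R2 | Reported SE too wide by | Type I error, omitted | Power, omitted | Power, included |
|---|---|---|---|---|
| 0 | 0% | 0.050 | 80.0% | 80.0% |
| 0.02 | 1.0% | 0.048 | 80.2% | 80.8% |
| 0.05 | 2.6% | 0.044 | 80.6% | 82.0% |
| 0.10 | 5.4% | 0.039 | 81.3% | 84.0% |

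The gain in power is 0, 0.6, 1.4 and 2.7 percentage points.

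**Simulation check.** 108 patients, 8 strata, permuted blocks of 4 (assumed, as the block size is not given), 6000 replicates per setting:

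- R2 = 0.10, omitted: reported SE 0.167, actual sampling SD of the estimate 0.158, type I error 0.040, power 80.5%.
- R2 = 0.10, included: reported SE 0.158, actual SD 0.157, type I error 0.049, power 83.4%.
- R2 = 0.05: power 79.7% omitted, 81.3% included.
- R2 = 0.10, true effect 0.467: mean estimate 0.465 omitted and 0.466 included, so no sign of bias either way.

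The actual sampling SD is almost the same in the two models. What differs is the standard error that the model reports.

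**The case against.** The case for leaving the ANCOVA alone has real content. The model already includes the pretreatment score, probably its most useful covariate. The error, if any, is on the safe side. The Power calculation rests on a repeated-measures ANOVA with no covariates mentioned, so omitting the two factors gives up extra power and does not push the trial below its planned 80%. The prognostic strength of gender and chronicity is unknown, and with R2 = 0 nothing is lost. All of this stands and keeps the point small. None of it explains why one stratification factor is kept and two are dropped.

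Three stronger readings are tempting, and the article does not support them.

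- A reader might infer that stratification on chronicity failed, because "each allocation was given to the recruiting RA in a sealed envelope prior to seeing a new patient". But the Blinding section says the envelope was opened only once the patient was included, and Patients recruitment places the eligibility interview and intake battery before randomisation. Chronicity could have been known by then. How envelopes were organised by stratum is not described, which is ordinary for an article.
- A reader might put the gain at 2 to 4 points, comparing 82.0% and 84.0% with a flat 80%. That does not fit with balanced strata, the premise behind the conservative type I error. Under balance the omitted model itself has 80.6% and 81.3%.
- A reader might count the missing covariates of the repeated-measures ANOVA and the mixed models as further errors. Those are silences that a full plan may fill; only the ANCOVA list is fixed here.

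**Conclusion.** The mismatch is in the text and the point holds in a limited form: the stated ANCOVA omits gender and chronicity although allocation was stratified on both. If they are prognostic beyond pretreatment score and age, reported standard errors are too large and the test is conservative. There is no bias and no inflation of the type I error.

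Over an assumed R2 of 0 to 0.10, the excess in the reported standard error runs from 0% to 5.4% and the power forgone from 0 to 2.7 points. These figures rest on the assumed R2, on balance having been achieved within strata, and on 80% power at 108 patients as the reference. The point does not threaten the validity of the trial. It is a free improvement, since the analysis can be matched to the design at almost no cost.

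**What to change.** In Data analysis, specify the short-term ANCOVA with treatment, pretreatment score, age, gender and chronicity, using the values recorded at baseline. For consistency, carry the same covariates into the long-term mixed models. If gender and chronicity are to stay out, give the reason.

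The cost is one line of text and two degrees of freedom: with 108 patients, residual degrees of freedom fall from 108 − 4 = 104 to 108 − 6 = 102. No new data are needed, because all three factors were required for randomisation. Patients recruitment describes recruitment as closed with follow-up continuing, so the change affects only the analysis text and should be fixed before the outcome is compared between arms.
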